#### 3.2. Secondary objectives

The secondary research questions that this study intends to answer are the following:

Does cardiac function differ postoperatively in a recipient who has received a donor heart with a functional impairment compared to a recipient who has received a donor heart with normal function?

With a systematic consideration of hearts with impaired function, by how much do the number of heart transplantations increase and how much faster can a patient be transplanted?

Does cardiac function in the donor affect cardiovascular events over time in the heart-transplanted patients?

Using cardiac biomarkers, ECG, echocardiographic imaging, and clinical data, can it be predicted early on which hearts will improve/recover function during the donation process?

Using cardiac biomarkers, ECG, echocardiographic imaging, and clinical data, can cardiac dysfunction caused by primary heart disease be ruled out?

Do donor hearts with dysfunction have different histology and/or biochemistry?

### 3.3. Primary variable

The primary variable is: Death, retransplantation or need of a mechanical assist one year after heart transplantation.

### 3.4. Secondary variable

The secondary variable is: frequency of left-sided moderate or severe primary graft dysfunction (PGD).

Moderate PGD is defined as having *at least one of the following at 24 hours after cross-clamp release*:

- Ejection fraction  $\leq 40\%$ , *or* hemodynamic compromise with right atrial pressure (RAP)  $> 15\text{mmHg}$ , pulmonary capillary wedge pressure  $> 20\text{mmHg}$ , cardiac index  $< 2.0$ , hypotension with a mean arterial pressure  $< 70\text{mmHg}$   
*And at least one of the following:*
- High-dose inotropes (Inotrope score  $> 10$ ) *or* newly placed intra-aortic balloon pump.

Severe PGD is defined as dependence on left or biventricular mechanical support in the form of either ECMO, LVAD, BiVAD, or percutaneous LVAD at 24 hours after cross-clamp release.

The following outcome variables apply to the secondary research questions:

Need for interventions and complications in the postoperative course including, for example, mechanical heart pump, intra-aortic balloon pump, need for mechanical ventilation, need for dialysis, dose and time with inotropic and vasoactive medications.

Occurrence of ICD codes for cardiovascular disease in the Patient and Cause of Death registries for participating patients at 3, 5, and 10 years after transplantation.

Levels of cardiac biomarkers, occurrence of specific echocardiographic changes, ECG changes, and clinical data in donors with recovered and non-recovered cardiac function during the donation process, respectively.

Levels of cardiac biomarkers, occurrence of specific echocardiographic changes, ECG changes, and clinical data in donors with primary and non-primary heart disease, respectively.

Estimation of the number of extra patients who would be able to receive a heart transplantation with a systematic utilization of donor hearts with dysfunction.

Presence of specific histological changes and specific proteins in heart tissue with dysfunction and normal function, respectively.

## 4. Study design and procedures

### 4.1. Overall study design

This is a non-randomized study.

The study consists of two protocols, one for the possible donors and one for the heart recipients. The heart function of the donor is systematically investigated according to the assessment protocol. The heart recipient is followed up according to clinical routine. Participation in the study will not affect what organ is allocated to the recipient. This procedure is according to clinical routine. The respective sections are presented below.

#### *Assessment of donor hearts (Attachment 1)*

For a possible donor to be relevant to the study, they must meet the following criteria. (1) The person shall be identified as a possible donor, (2) next of kin should have been informed about futile prognosis and transition to end-of-life care, (3) the person shall fulfill criteria(s) for being positive to organ donation according to national guidelines / local regulations and (4) the transplantation coordinator / center have been contacted. For a possible donor where all criteria are met, an ultrasound examination of the heart is planned as soon as it is suitable and logistically possible. In cases where the donation process proceeds, cardiac examination follows the protocol (Figure 1). This can briefly be described in three different scenarios.

- Scenario 1: If the UCG shows normal cardiac function, the heart is accepted for transplantation in the usual way.
- Scenario 2: If the UCG shows ejection fraction < 50%, an assessment of whether the cardiac function is acceptable according to set recommendations (see below) is performed. If the function is not considered acceptable, echocardiography is repeated when practically feasible. An improvement in ejection fraction could be expected after 12 hours. This can be repeated several times, until the donation process ends.
- Scenario 3: If the UCG shows regional hypokinesia and coronary artery disease cannot be ruled out clinically, a coronary angiogram or CT-heart is performed. If the coronary angiogram excludes coronary artery disease, assessment of the cardiac function is done according to scenario 2.

At each UCG, investigations with ECG and blood tests for cardiac biomarkers (troponin T, NTproBNP) are performed. Clinical data will be recorded from the actual care event and during the donation process.

#### *Recommendations for accepting marginal hearts:*

- Ejection fraction shall be over 40%
- Improvement (but not necessarily normalization) of cardiac function should be observed. The study recommends an improvement in ejection fraction of 10% to be significant.

- Regional wall motion abnormalities are not in themselves a contraindication for heart transplantation, unless coronary artery disease is excluded according to clinical guidelines or with coronary angiogram.
- In cases with borderline ejection fraction (slightly below 40%), inotropic support may be given to evaluate the reversibility of cardiac function (test with inotropes).
- Cardiac biomarkers with relatively low troponin values that are decreasing, and high NTproBNP is supportive for a decision to transplant the heart.

These recommendations are based on the retrospective studies available. The protocol ensures that the cardiac dysfunction observed is a dynamic and reversible process. The recommendation of having an increase in ejection fraction of 10% to be considered significant reduces the risk of misassessments. The decision for transplantation of the donor heart remains with the responsible thoracic surgeon, as there may be additional factors that the study protocol cannot take into account. In such cases, these will be documented.

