However, cardiac dysfunction in organ donors is usually secondary to the disease that led to brain death and is generally reversible, i.e., there is nothing wrong with the heart itself but it has been exposed to an unfavorable environment that temporarily affects its function. A common cause of cardiac dysfunction in organ donors is stress-induced cardiomyopathy/Takotsubo cardiomyopathy. Stress-induced cardiomyopathy is a relatively newly described acute cardiac syndrome in which the heart develops regional wall motion abnormalities caused by severe catecholamine stimulation of the myocardium. In organ donors, a strong catecholamine storm is observed with brain herniation and the development of brain death, which can trigger stress-induced cardiomyopathy. This type of change is seen in 20-25% of potential organ donors. One of the most important characteristics of stress-induced cardiomyopathy is its rapid recovery, however, and cardiac function is usually normalized within a few hours or days. This is not only seen as a functional recovery, but also a structural and biochemical recovery of the heart. In addition to organ donors with intracranial events, stress-induced cardiomyopathy is also seen in patients with hypoxic/anoxic brain injuries as a result of hypoxic cardiac arrest, and even in these cases, cardiac events are temporary.

There are potentially differential diagnoses for stress-induced cardiomyopathy in potential donors. The most important is ischemic heart disease which can quickly and relatively easily be diagnosed with coronary angiography. Coronary angiography is performed today on approximately one-third of potential donors and then primarily on donors with a risk profile for coronary artery disease. Another different diagnosis is myocarditis, which does not have the same reversibility as stress-induced cardiomyopathy and usually have a different echocardiographic pattern.

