#### 3.1. Primary objective

The primary objective is to investigate whether recipients of donor hearts with regional wall motion abnormalities and/or mild to moderate globally reduced cardiac function have the same outcome as recipients of hearts with normal function.

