## 7.2. Statistical analyses

### 7.2.1. Statistical methods

The primary variables will be analyzed with binary logistic regression. The primary outcome variable will be incidence of death, re-transplantation or need of long-term mechanical assistance within one year after transplantation. The primary explanatory variable is incidence of cardiac dysfunction in the donor, defined as regional hypokinesia and/or ejection fraction < 50%. The analysis will be adjusted for age of recipient, age of donor, need of mechanical assistance before transplantation and "urgent call" status of transplantation.

For statistical significance, the p-value must be  $> 0.05$ .

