## 14. Attachments

Attachment 1. Assessment protocol for heart donors (Utredningsprotokoll för donatorer)

Attachment 2. List of variables

Attachment 3. Study visit scheme

[figure not shown]

a Preferably made at least six hours apart

b -- Donor age:

- < 45 yo preferable
- 45-50 yo if ischemic time < 4 hrs
- > 55 yo only if survival benefit exceeds the decrement in early HT survival

-- Donor size:

- If body weight in donor is not  $\geq 30\%$  less than recipient's, its is uniformly safe.
- If female donor, use with caution if donor body weight is  $\geq 20\%$  less than male recipient donor weight 

-- Donor comorbidities and cause of death

c Ischemic time should be  $\leq 4$  hrs. If greater other factors in donor and recipient should be ideal 

CAD: Coronary artery disease, EF: Ejection Fraction, RWMA: Regional Wall Motion Abnormalities.

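### The acceptance recommendation for donor hearts with regional wall motion abnormalities states its coronary artery disease condition backwards and conflicts with Scenario 3

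*Protocol*

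**What the plan says.** Section 4.1 handles regional wall motion abnormalities in two places.

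- **Scenario 3** of the donor assessment gives the work-up: "If the UCG shows regional hypokinesia and coronary artery disease cannot be ruled out clinically, a coronary angiogram or CT-heart is performed". It then gives the consequence of a clear result: "If the coronary angiogram excludes coronary artery disease, assessment of the cardiac function is done according to scenario 2". Scenario 2 in turn judges the heart's function against the recommendations listed further down the same section.
- **The recommendations for accepting marginal hearts**, five bullets in all, include this one: "Regional wall motion abnormalities are not in themselves a contraindication for heart transplantation, unless coronary artery disease is excluded according to clinical guidelines". The sentence ends by naming coronary angiography as the other way of excluding disease. Below the bullets, the protocol adds: "The decision for transplantation of the donor heart remains with the responsible thoracic surgeon".

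Three other sections show what is intended. Section 1 discusses alternatives to stress-induced cardiomyopathy and says: "The most important is ischemic heart disease which can quickly and relatively easily be diagnosed with coronary angiography". Section 3.1 asks whether "recipients of donor hearts with regional wall motion abnormalities and/or mild to moderate globally reduced cardiac function have the same outcome" as recipients of normal hearts. Section 7.2.1 has donor dysfunction "defined as regional hypokinesia and/or ejection fraction < 50" percent.

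**The concern.** In Scenario 3, exclusion of coronary disease is what lets a heart with a regional abnormality go forward. In the recommendation, the same exclusion is the exception to acceptability. The two point in opposite directions, and Scenario 3 leads, through Scenario 2, to the very list that contains the faulty bullet. A heart just cleared of coronary disease is therefore judged against a rule that reverses the condition it has met.

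The matter at stake is donor acceptance. Followed to the letter, the bullet raises no objection to a heart whose wall motion abnormality might be ischaemic and whose coronary arteries have not been cleared. The protocol rests its safety argument on these recommendations: section 1 expects recipient outcome to be unaffected if they are followed, and section 3 makes safety depend on the heart being investigated and its impairment falling within the study's guidelines. In a multicentre study, sites should be able to rely on the wording of that list.

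**Working it through.** No figure in the protocol bears on this point, so the check is one of logic.

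**Step 1: what the bullet asserts.** Let A be *the wall motion abnormality is a contraindication* and B be *coronary artery disease has been excluded*. The bullet has the form *not A, unless B*.

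- Strict logic gives: if not B, then not A. While disease has not been excluded, the abnormality is not a contraindication.
- Ordinary usage usually adds: if B, then A. Once disease has been excluded, the abnormality is a contraindication. Strict logic does not force this second half.

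**Step 2: comparison with Scenario 3.**

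| Regional abnormality and... | Recommendation as written | Scenario 3 |
|---|---|---|
| disease not excluded | No contraindication (strict logic) | Coronary angiogram or CT first where disease cannot be ruled out clinically |
| disease excluded | Contraindicated (ordinary reading); silent (strict logic) | Proceeds to functional assessment under Scenario 2 |

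In the first row the bullet drops the coronary condition that Scenario 3 imposes. In the second, the ordinary reading of the bullet is the reverse of Scenario 3. Under strict logic the bullet says nothing in the one case where Scenario 3 lets the heart proceed.

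**Step 3: which direction is intended.** Section 1 names ischaemic heart disease as the most important alternative diagnosis, which is a reason to exclude it before transplanting. Section 3.1 makes recipients of hearts with regional abnormalities part of the primary comparison, and section 7.2.1 counts regional hypokinesia as exposure. A rule that turned such hearts down after coronary disease had been excluded would not fit that objective. Scenario 3 therefore has the direction right, and the bullet has it wrong.

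**Step 4: does the correction remove the conflict?** With *provided that*, the bullet says that the abnormality is not a contraindication if disease has been excluded, which agrees with the second row of Scenario 3. In ordinary reading it also withholds that assurance while disease has not been excluded, which agrees with the first row. Both discrepancies go.

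**The case against.** The strongest reply is that this is a language slip and not a clash of operative rules.

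- The bullet concerns whether a wall motion abnormality is in itself a contraindication. Scenario 3 concerns which investigation to perform, and it does not say that a heart with unexcluded disease is contraindicated. On strict logic a site could hold the bullet true and still carry out the imaging. Head-on opposition needs the ordinary reading of *unless*.
- The intent can be recovered from Scenario 3, which comes just before the list. It is implausible that a transplant surgeon would decline a heart because its coronary arteries are clear.
- The bullets are recommendations, the surgeon decides, and section 4.1 says that study participation does not affect which organ a recipient is allocated.
- The Attachment 1 flow chart, which sites may work from, is not visible. Its legend in section 14 reads "CAD: Coronary artery disease, EF: Ejection Fraction, RWMA: Regional Wall Motion Abnormalities", so it probably covers this step and may state it correctly.

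Most of this stands, and it is why the point is minor. It does not make the sentence right. Even on the strict reading, the bullet gives its assurance in the case that Scenario 3 sends for imaging and withholds it in the case that Scenario 3 lets through. No other visible text corrects the bullet. A clear intent elsewhere is a reason to correct the sentence easily, not a reason to leave it.

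**Conclusion.** The concern holds, as a minor error. One word in one of the five acceptance recommendations reverses the coronary condition and puts the bullet at odds with Scenario 3.

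That the bullet clears hearts whose coronary status is unsettled follows from its wording alone. That it also rules out hearts with coronary disease excluded rests on the ordinary reading of *unless*; the conclusion does not need it.

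The practical risk is small. The numbers to be included (445 transplanted, at least 89 with impaired hearts), the definition of donor dysfunction and the planned analysis are untouched, and the protocol shows no heart handled on the literal wording. How the flow chart states the rule could not be checked.

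**What to change.** In the third recommendation, replace *unless* with *provided that* and leave the rest of the sentence as it is, including both routes to exclusion (clinical guidelines or coronary angiogram). Check that the Attachment 1 flow chart states the step in the same direction, and send sites a short note of the correction.

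The cost is one corrected word, one check and one notice. Sample size, exposure definition, analysis and data collection do not change.

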#### *Follow-up of recipients*

Recipient baseline data, including demographics and medical history, is recorded at inclusion. The recipients will be followed regarding death, need of mechanical heart pump and re-transplantation during the first year (primary outcome variable). Short-term data will be collected regarding need of post-operative mechanical assistance, intra-aortic balloon pump, dialysis, time with mechanical ventilation, inotropic drugs, re-surgery(s), time at the ICU, time at the home clinic/other department, time before returning home. The recipients will be followed according to clinical routine at the participating center, and no extra examinations are planned, with the exception that echocardiography is preferable performed at  $24 \pm 6$  hours for assessment of PGD.

The active follow-up end at one year after transplantation. Long-term complications that will be followed are death, need for mechanical heart pump, re-transplantation, rejection/coronary vasculitis, other organ failure. To investigate whether recipients of hearts with dysfunction have increased risk for other disease, data will be collected from the Swedish National Board of Health and Welfare's (Socialstyrelsen) Patient Register and Cause of Death Register. Those data that will be requested are all of the patients' ICD codes and medical procedure codes at 1, 3, 5, and 10 years after transplantation. Data may be collected from other national registers if they are available.

A list of variables is available in *Attachment 2*.

## 4.2. Procedures and flow chart

Follow-up is done according to clinical routine at each participating center with the exception that echocardiography is preferable performed at  $24 \pm 6$  hours for assessment of PGD. A study visit scheme is available in *Attachment 3*.

Data will be collected from the donor during the donation process. Data from recipients will be collected at the following time points: at inclusion, at the time of transplantation, 24 hours post-transplantation, at discharge from the intensive care unit (can be repeated upon readmission), at

discharge from the hospital, SAE monitoring up to 28 days, mortality follow-up at 3 and 6 months, and at one year post-transplantation.

Instructions to register data follows below:

### **Pre-op Data / Transplantation**

- The data recorded is the data that forms the basis for the decision to transplant. This is particularly important for echocardiography, cardiac catheterization, VO2 max, and GFR, where multiple examinations may exist. Typically, the examinations closest to the transplantation decision are used.
- If the patient is accepted for mechanical assist as a bridge-to-transplant, the data underlying the bridge-to-transplant decision is registered.
- For patients receiving mechanical assist prior to the initiation of the transplantation evaluation (e.g., in cases of acute need for mechanical assist, i.e., "bridge-to-decision"), echocardiography, cardiac catheterization data, and GFR/eGFR before mechanical assist are registered, if available. If not available, the data in closest proximity to mechanical assist is registered.
- For GUCH (Grown-Up Congenital Heart) patients, the available data is recorded. The ejection fraction for the systemic ventricle is reported.

### **At Transplantation**

- The data registered is that which is available closest to the time of transplantation. For echocardiography, cardiac catheterization, VO2 max, and GFR, the data closest to transplantation is registered. If no new data has been collected since acceptance for transplantation, no new data needs to be registered.
- For patients with mechanical assist, echocardiography data is not registered. Cardiac catheterization data is registered at the baseline speed setting. Register the data available, noting that dilated values are typically not present. Pressure values are more important than cardiac output (PVR, PCWP, mPAP, CVP, TPG). GFR/eGFR is registered if available.
- Ischemic time is defined as the time from flushing to "cross-clamp release." For hearts that have used a heart box, both total ischemia time and time in the box are registered.
- Cross-clamp release marks the time of transplantation. The date and time are recorded from this point.

### **24 Hours After Transplantation**

- If data is missing at the 24-hour mark, data is registered as close as possible to 24 hours, with the following exceptions:
  - Data from a pulmonary artery catheter is valid within  $\pm 6$  hours of the 24-hour mark. Values outside this range are considered "missing."

- The first echocardiography is registered in the eCRF under a separate heading. The date and time of the examination are recorded.

#### **At Discharge from ICU**

- For ICU interventions (e.g., time with mechanical ventilation, CRRT etc.), any day with an intervention, regardless of how brief it is, is counted as a full day of treatment.
- The ICU discharge form is repeated upon readmission to the ICU.
- Register the echocardiography data as close as possible to discharge from the ICU. If the echocardiography performed at ICU discharge is the same as that performed at 7–14 days, it does not need to be registered again.

#### **Echocardiography at 7–14 Days Post-Transplantation**

- The acceptable range for echocardiography is 7 to 14 days post-transplantation. If no echocardiography is performed during this period, the value is recorded as "missing."
- If multiple echocardiography results are available, register the one closest to 7 days post-transplantation.
- Basic echocardiography, such as screenings for pericardial effusion, does not need to be registered. If only such echocardiography is available within this period, register the data that is available; typically, ejection fraction or heart function is reported.

